### Outcome Measures

#### Demographic Characteristics of the Study Population

Major obstetrical risk factors were registered. Moreover, GA, birth weight, length and head circumference, gender, Apgar scores, inborn or transferred, days of mechanical ventilation, and days of extra oxygen were registered.

#### Clinical Outcomes

To determine the safety and tolerability of BC feeding, clinical outcomes were recorded. They included the presence of feeding intolerance (defined as at any time when feeding was withheld by the neonatologists from day 1–7 and from day 8–14), characteristics of gastric residuals, stool characteristics (all measured daily for the first 2 weeks), and any suspicion or treatment of NEC. Furthermore, bronchopulmonary dysplasia, retinopathy of prematurity, intraventricular hemorrhage, and periventricular leukomalacia diagnosed at discharge were recorded. Growth and nutritional data including weekly anthropometric measures [body weight (BWT), length, and head circumference], days to regain birth weight, days on PN, time to full enteral feeding, and nutritional intake were also recorded. In phases A and B, time to full enteral feeding was defined according to the guideline of each hospital, i.e., as the first day an infant received 160 ml·kg^−1^·day^−1^ at RH, or 120 ml·kg^−1^·day^−1^ at FWCH for a consecutive period of 72 h. Based on the experiences from phases A and B, full enteral feeding volume will be defined as 150 ml·kg^−1^·day^−1^ for all sites in phase C to have a uniform definition.

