#### Nutritional Guidelines at FWCH and SBMCH (China)

At FWCH and SBMCH, feeding was normally initiated within 48 h after birth with a volume of 5–10 ml·kg^−1^·day^−1^ and advanced with a rate of 10–20 ml·kg^−1^·day^−1^. The volume of full enteral feeding was defined as 120 ml·kg^−1^·day^−1^, and supplementary PN was used until infants reached this volume. When MM was absent, or not available in adequate amounts, IF (SSC 81; Abbott Laboratories, Abbott Park, IL and Enfamil A+, Mead Johnson) was used. Fortification (Similac Human Milk Fortifier, Abbott Nutrition) of MM began when the infants could take 80 ml·kg^−1^·day^−1^ enterally.

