#### Randomized Phase C

Outcomes from phase C will be compared for Denmark and China separately. Outcomes between BC group and the control group will be compared without knowing the group designation code. Continuous outcomes, e.g., levels of plasma amino acids, will be compared using general linear models with adjustment for potential confounders, e.g., birth weight, GA, study site, and gender. Data will be checked for normality and homoscedasticity and will be transformed when required. For binary outcomes, e.g., presence of feeding intolerance, generalized linear models will be used with adjustment for potential confounders. *p* < 0.05 is considered as statistically significant.

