### Nutrition and Clinical Outcomes at Danish Site (RH)

Bovine colostrum was given as the first diet on day 1 for a total of 7 ± 3 days, amounting to a total volume of 273 ± 199 ml (Table 3). During the days, BC was given, 22 ± 11 ml·kg^−1^ was fed providing 1.81 ± 0.89 g·kg^−1^ protein per day. Two infants with birth weights <1,000 g received parenteral nutrition for 11–13 days, but the remaining infants received only enteral nutrition. During the first week of life, the infants received 97 ml·kg^−1^·day^−1^ fluid, 3.4 g·kg^−1^·day^−1^ protein, and 69 kcal·kg^−1^·day^−1^. BC accounted for on average 23% of fluid, 54% of protein, and 26% of energy intakes, with the remaining deriving from MM, DM, and parenteral nutrition (Figure 2). In week 2, fluid and energy intakes increased to 161 ml·kg^−1^·day^−1^ and 114 kcal·kg^−1^·day^−1^, whereas protein intake remained the same as in week 1 (Figure 2). Time to regain birth weight was 12 ± 2 days, and time to reach full enteral feeding (160 ml·kg^−1^·day^−1^) was 22 ± 1 (Table 3). Four RH infants received 150–160 ml·kg^−1^·day^−1^ for a relatively long period. When 150 ml·kg^−1^·day^−1^ was used as the cut-off, the time was only 9 ± 3 days. GV was negative in the first week, increased throughout weeks 2–3 and decreased in week 4 (Figure 2). Feeding intolerance was observed in six infants during the first week and in one infant in week 2. Total volume of gastric residuals was 80 ± 41 ml (10.8% of enteral nutrition) in the first week (Table 3).

**Table 3 T3:** **Outcomes of the first infants to receive BC as supplement to maternal milk in the first days of life**.^a^

	RH	FWCH
*N*	4–7	4–5
Days on PN (days)	3 ± 6	22 ± 9
BC feeding (days)	7 ± 3	7 ± 1
Total BC intake (ml)	273 ± 199	234 ± 92
TTF160 (days)	22 ± 11	ND
TTF120 (days)	8 ± 3	21 ± 8
FI in week 1, *n*	6	1
FI in week 2, *n*	1	0
GR in week 1 (ml)	80 ± 41	5 ± 5
Body weight at 37 weeks/discharge (g)	2,492 ± 326	2,138 ± 176
GA at 37 weeks/discharge (weeks)	37.3 ± 0.5	35.9 ± 0.8
*Z*-score at 37 weeks/discharge	−1.3 ± 0.7	−1.3 ± 0.6
*Z*-score change	−1.2 ± 0.6	−0.5 ± 0.5
GV (g·day^−1^)	22.0 ± 4.6	23.1 ± 5.0
GV (g·kg^−1^·day^−1^)	11.8 ± 0.9	12.9 ± 2.7
Regain birth weight (days)	12 ± 2	6 ± 2
Hypertyrosinemia on day 7, *n*	3	2
Tyrosine on day 7 (μmol·l^−1^)	171 ± 200	197 ± 163
BUN on day 7 (mmol·l^−1^)	5.8 ± 3.3	3.3 ± 1.1
BUN on day 14 (mmol·l^−1^)	2.0 ± 0.3	1.7 ± 0.6

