The Chinese sites and Danish sites also differed in the feeding regimens according to their use of nutritional guidelines. The Chinese sites started enteral feeding within 48 h and increased the volume slowly by 10–20 to 120 ml·kg^−1^·day^−1^ as the target full enteral volume. The Danish site normally started enteral feeding within 2–6 h after birth and increased the volume as fast as the infants could tolerate to 160 ml·kg^−1^·day^−1^ as the full enteral volume. We did not consider it possible or appropriate to standardize the feeding regimens.

In conclusion, we suggest that BC may be a relevant alternative milk diet to DM or IF as a supplement to MM in the first days of life in preterm infants. The Precolos trial is the first step to document this novel method. If Precolos can demonstrate that early BC supplementation is well tolerated, feasible, and supports one or more of the multiple outcomes to be measured in phase C, then this paves the way for a larger randomized clinical trial. Clinically relevant outcomes of such a larger trial will be intestinal functions (e.g., feeding intolerance and intestinal permeability), time to full enteral feeding, growth, length of hospital stay, NEC, and sepsis.

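### Phase C times full enteral feeding to 150 ml/kg/day at every site, but the Chinese target is 120 and nothing in the protocol says Chinese feeds go beyond it

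*Protocol article*

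**What the plan says.** **Outcome definition (Clinical Outcomes).** In phases A and B, time to full enteral feeding followed each hospital's own guideline: 160 ml/kg/day at RH and 120 at FWCH, with a 72 h requirement. For phase C: "Based on the experiences from phases A and B, full enteral feeding volume will be defined as 150" ml/kg/day, and this applies "for all sites in phase C to have a uniform definition".

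**Chinese practice (Nutritional Guidelines at FWCH and SBMCH).** "The volume of full enteral feeding was defined as 120" ml/kg/day, and "supplementary PN was used until infants reached this volume". The Discussion repeats it: "The Chinese sites started enteral feeding within 48 h and increased the volume slowly by 10–20 to 120" ml/kg/day, which it describes as the target.

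**Phase C practice.** Under BC Regimen, the intervention group is fed as in phases A and B, where volume followed the hospital guideline. Controls get each site's standard diet. The Discussion adds: "We did not consider it possible or appropriate to standardize the feeding regimens".

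**Analysis (Randomized Phase C).** "Outcomes from phase C will be compared for Denmark and China separately". General linear models are named for continuous outcomes and generalized linear models for binary ones.

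**Pilot results.** At RH, when 150 ml/kg/day "was used as the cut-off, the time was only 9 ± 3 days". For FWCH, Table 3 gives time to 120 as 21 ± 8 days and ND for time to 160. No FWCH time to 150 appears anywhere.

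**The concern.** The phase C threshold sits above the volume that the Chinese sites aim for and below the Danish target of 160. Nothing in the article says that Chinese feeds are advanced to 150. Whether and when a Chinese infant reaches it then depends partly on what clinicians choose to do after the local goal is met. Phase C is open label, so those choices can be made knowing the allocation.

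Two features add to this. Figure 1 ends the Chinese BC period at day 14, while time to 120 already averaged day 21 at FWCH, so a higher threshold moves the outcome further from the intervention. And an infant who never reaches 150 has no observed time. If such infants were left out of a linear model, the slowest feeders would be the ones removed.

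The stake is the pilot's second objective, to help choose endpoints and sample size for a larger trial. The Discussion lists time to full enteral feeding among that trial's relevant outcomes. An unclear Chinese estimate would feed straight into that choice.

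**Working it through.** The article states no attainment rate, power or sample-size figure for this outcome, so there is nothing to reproduce. The check compares the sections and then uses illustrative arithmetic.

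**1. Gap to the local target.** 150 − 120 = 30 ml/kg/day, which is 30/120 = 25% above the Chinese target. Against the Danish target, 150 is 10 below 160.

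**2. Extra time from 120 to 150, if advancement continues.** At the guideline step of 10–20 ml/kg/day: 30/20 = 1.5 days to 30/10 = 3 days. That advancement does continue is an assumption.

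**3. Observation window at FWCH.** Mean gestational age is 31.8 weeks at birth (Table 2) and 35.9 at 37 weeks/discharge (Table 3): (35.9 − 31.8) × 7 = 28.7 days.

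**4. Share not yet at the volume by day 28.7.** Normal model, P = 1 − Φ((28.7 − mean)/SD), with mean 21 for 120 and 22.5–24 for 150. The SD is 8 (Table 3), or √(8² + (0.8 × 7)²) ≈ 9.8 if the spread of gestational age at discharge is added.

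| Volume | SD 8 | SD 9.8 |
|---|---|---|
| 120 | 1 − Φ(7.7/8) = 0.17 | 1 − Φ(7.7/9.8) = 0.22 |
| 150, +1.5 days | 1 − Φ(6.2/8) = 0.22 | 1 − Φ(6.2/9.8) = 0.26 |
| 150, +3 days | 1 − Φ(4.7/8) = 0.28 | 1 − Φ(4.7/9.8) = 0.32 |

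Moving from 120 to 150 therefore adds about 5–11 percentage points, or 0.5–1 infant in an arm of about 10 (20 Chinese infants randomised 1:1).

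**5. Sensitivity.**
- The FWCH results text gives time to 120 as 22 ± 11 days, not 21 ± 8. With that, 0.27 are not at 120 and 0.32–0.37 not at 150. The two figures conflict; 22 ± 11 is also Table 3's entry for time to 160 at RH.
- Adding 3 days for completion of 72 h raises both thresholds: 120 to 0.28–0.32 and 150 to 0.34–0.43.
- Starting on day 2 at 5 ml/kg/day and reaching 120 on day 21 implies (120 − 5)/(21 − 2) ≈ 6 ml/kg/day, slower than the guideline. At that pace the last 30 takes about 5 days, and 1 − Φ((28.7 − 26)/8) ≈ 0.37 are not at 150, about 20 points above 120.
- If feeds stop at 120, 100% are not at 150. No section says they stop.

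**6. Sensitivity to the cut-off in the pilot's own data.** At RH the mean was 9 days at 150 and 22 days at 160 (22 ± 11 in Table 3; the text prints 22 ± 1), with four infants held between the two for a relatively long period. A small shift in threshold near where feeds level off can move the outcome greatly. Table 3 covers 4–7 RH infants, so the two means may not rest on the same infants.

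**The case against.** Several parts of the opposing case stand.

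- **Non-attainment is not documented.** A reader might infer that Chinese infants often never reach 150. No FWCH time to 150 is reported. The ND in Table 3 concerns 160 and is not explained there (under Table 1 it means not determined). Nor does the FWCH week 2 intake of 153 ml/kg/day prove the opposite: it counts fluid from all sources, while PN lasted 22 ± 9 days.
- **120 is a target, not a ceiling.** A reader might infer that Chinese feeds halt there. The text makes it the goal and the point where PN ends, and says nothing about holding volumes.
- **Local policy does not confound the comparison.** A reader might infer that the outcome measures site policy instead of BC. Arms are randomised and compared within country, so both share the policy. What remains is lost sensitivity, possible censoring, and discretion in an open-label setting.
- **Most of the modelled shortfall is already there at 120**, as step 4 shows.
- **A common definition has a use.** It serves the planning of a multicentre trial even when countries are analysed apart, and the RH data give a reason to leave 160. Replacing 150 with 120 would be a matter of preference, and 120 is itself tied to local policy.
- **The linear model is not assigned to this outcome.** The article's example is plasma amino acids. Handling of infants who never reach the volume may sit in an analysis plan that is not shown, so its absence is not an error.

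The objection does not remove the mismatch itself. The article justifies 150 by pilot experience and reports such experience only for Denmark, and no section connects 150 with the retained Chinese target.

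**Conclusion.** The point holds as an unreconciled outcome definition: 150 at all sites, against a Chinese target and PN end-point of 120 under regimens left to local practice. In China the outcome may be unreached by some infants or turn on advancement past the local target.

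The size is unknown. At guideline speed, 150 adds about 5–11 points of non-attainment to the 17–22% modelled at 120; at the slower pace implied by the pilot it adds about 20 points; and only if feeds stop at 120 is it 100%. All of this rests on 4–5 infants, a normal distribution, continued advancement, and feeding time being independent of length of stay. If slow feeders stay longer, the shares are too high. The SD of 9.8 also treats the spread of gestational age at discharge as the spread of postnatal day, ignoring the 1.6-week SD at birth.

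Severity is minor to moderate. No primary endpoint is set, and this is one of many outcomes.

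**What to change.** 1. In Clinical Outcomes, state how the 150 ml/kg/day definition relates to the 120 target in the Chinese guideline and the Discussion. This concerns the outcome definition only and changes no feeding practice.
2. Keep 150 as the uniform phase C outcome, and also report time to 120 ml/kg/day sustained for 72 h at all sites. Time to 120 was obtained at both sites in phases A and B (8 ± 3 days at RH, 21 ± 8 at FWCH) and can be derived from recorded intake.
3. Analyse both as time-to-event, with infants who do not reach the volume censored at discharge or end of follow-up. Report their number by arm and country, since discharge may itself depend on feeding progress.
4. Reconcile the two FWCH figures for time to 120 (21 ± 8 and 22 ± 11 days) before either is used for planning.

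The cost is wording and one more secondary outcome in a pilot that already has many. No new data collection is needed if daily enteral volumes are recorded up to discharge.

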#### Paraclinical Outcomes

In phases A and B, safety measures including plasma amino acid composition, routine blood biochemistry tests, and levels of intact bovine IgG (bIgG) in plasma were measured on days 7 ± 1 and 14 ± 1. Intact bIgG molecules were quantified by electroimmunoassay (lower detection limit, 5 μg·ml^−1^) using purified bIgG as the standard and anti-bIgG as the antibody at Department of Biology, Lund University (21). In phase C, in addition to the above mentioned blood tests, a simplified three-sugar test will be performed on study day 7 ± 1 to assess intestinal function. In brief, an oral bolus containing 5% lactose, 5% lactulose, and 2% mannitol will be given to the study subjects. Blood samples will be taken at 40 min, and urine samples will be collected continuously for 6 h after administration. By analyzing the level of galactose (a digestive adduct of lactose) in blood and the ratios of lactulose/lactose and lactulose/mannitol in urine, lactose digestion, galactose uptake capacity, and intestinal permeability can be evaluated (22, 23). Fecal samples are collected on days 7 ± 1 and 14 ± 1 for fecal microbiota and short-chain fatty acid composition analyses in all three phases of the study.

### Sample Size

Fifty infants are planned to be recruited in the study: 3 in phase A, 7 in phase B, and 40 (20 + 20) in phase C. Since this study is a pilot feasibility study and no primary endpoint was set, the sample size was determined by practical considerations.

### Statistical Analysis

#### Phases A and B

Continuous variables were presented as means ± SD, and binary data were presented in counts. BUN levels measured on two different time points were compared for each hospital using paired *t*-test in Prism 5 (version 5.01, GraphPad software). Two types of growth velocity (GV) were calculated based on BWT measured weekly according to the following formulas: (1) GV (g·day^−1^) = (BWTDay *n* − BWTDay 1)/(Day *n* − Day 1) and (2) GV (g·kg^−1^·day^−1^) = [1,000 × ln(BWTDay *n*/BWTDay 1)]/(Day *n* − Day 1) (24). *Z*-score was calculated based on GA and weight using a gender specific reference (25) at birth and at 37 weeks or discharge. Day of regaining birth weight was recorded or calculated based on GV if not recorded.

#### Randomized Phase C

Outcomes from phase C will be compared for Denmark and China separately. Outcomes between BC group and the control group will be compared without knowing the group designation code. Continuous outcomes, e.g., levels of plasma amino acids, will be compared using general linear models with adjustment for potential confounders, e.g., birth weight, GA, study site, and gender. Data will be checked for normality and homoscedasticity and will be transformed when required. For binary outcomes, e.g., presence of feeding intolerance, generalized linear models will be used with adjustment for potential confounders. *p* < 0.05 is considered as statistically significant.

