### Recruitment and Randomization

When a preterm infant was delivered, or transferred from other hospitals on the day of birth, attending neonatologists or a clinical researcher would evaluate the infant for its eligibility. If the infant fulfilled the recruitment criteria, the parent(s) would receive written and oral information about the study. Infants were included in the study after written parental consent was given.

Preterm infants were included in this study since we could not study the effect of BC as the first enteral nutrition for preterm infants by including other patient populations. Parents were informed with great care and given consideration time before inclusion. Because inclusion had to be done within a fixed period of time, this consideration time was not unlimited. If the parents found the consideration time to be too short, we accepted this and did not ask for consent.

No randomization was needed for phases A and B. For phase C, recruited infants are randomized into a control group and an intervention group in a 1:1 ratio. Random sequences of groups are generated by a computer program with randomly permuted blocks of sizes 2 and 4, written on slips, and put in opaque envelopes individually by an employee of the study sponsor. An envelope can only be opened to see the allocation after an infant has been enrolled. If multiple births are recruited together, all of them will be allocated to the same group, which will be accounted for during the data analysis. A set of 20 envelopes with random sequences will be generated for RH and HH together and coordinated by the primary investigator (PI) of RH *via* telephone call, and the recruitment will stop when 20 infants in total have been enrolled. The PI of HH will call the PI of RH when an infant is recruited and the PI of RH will open the corresponding envelope and tell which group the infant should be randomized to. For FWCH and SBMCH, two sets of 20 envelopes will be generated (one set for each) due to the difficulties related to coordination by telephone conversation. The study sponsor will coordinate and stop recruitment at the two Chinese sites when 20 infants in total have been enrolled.

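### Covariate-adjusted models for binary outcomes within each country (about 10 v 10 infants) will often have no finite estimate; phase C needs a sparse-data method

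*Protocol article*

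**What the plan says.** The Sample Size section of the protocol article gives the total: "Fifty infants are planned to be recruited in the study: 3 in phase A, 7 in phase B, and 40 (20 + 20) in phase C". It gives no power basis: "Since this study is a pilot feasibility study and no primary endpoint was set, the sample size was determined by practical considerations".

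Recruitment and Randomization sets a 1:1 ratio and a cap for each country. For the two Danish hospitals, "the recruitment will stop when 20 infants in total have been enrolled". For China, "The study sponsor will coordinate and stop recruitment at the two Chinese sites when 20 infants in total have been enrolled".

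Under Statistical Analysis, Randomized Phase C, the comparison is made by country: "Outcomes from phase C will be compared for Denmark and China separately". Continuous outcomes use general linear models "with adjustment for potential confounders, e.g., birth weight, GA, study site, and gender". For binary outcomes the text is "For binary outcomes, e.g., presence of feeding intolerance, generalized linear models will be used with adjustment for potential confounders". The link function and the binary covariates are not named, and no method is given for sparse data. The threshold is p < 0.05.

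**The concern.** Each comparison rests on about 20 infants. The phase A and B results put the named binary outcome near the extremes in both countries, and NEC and sepsis at zero. An adjusted binary model on so few infants tends to separate: some combination of arm and covariates predicts the outcome perfectly for part of the sample, and the likelihood then has no finite maximum. Software may still print a very large coefficient and standard error, or a convergence warning, and neither is a usable estimate.

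The lack of a primary endpoint does not make these estimates dispensable. The Introduction's second objective is to help choose endpoints and sample size for a later trial. The Discussion ties the move to that trial partly to whether phase C shows the supplement to be well tolerated. An analysis that returns no between-arm estimate of feeding intolerance weakens both uses.

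**Working it through.** The plan's own numbers are consistent: 3 + 7 + 40 = 50, and 40 = 20 per country, so 1:1 gives about 10 v 10. Because siblings share an arm, the actual split may differ a little. There is no power figure to reproduce.

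**Inputs from the documents.** Feeding intolerance on bovine colostrum, from Initial Results and Table 3:
- Denmark: 6/7 in week 1, 1/7 in week 2.
- China: 1/5 in week 1, 0/5 in week 2.

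NEC and sepsis were 0/12 (Safety Outcomes).

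**Assumptions.**
- Logit link.
- A 5% rate where no event was seen.
- A control rate equal to the treated rate, then varied, because the documents give no control rate.
- Correlation 0.7 between birth weight and gestational age.
- Even splits for site and sex.

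**Arm alone.** With one binary predictor, the estimate is infinite or undefined whenever either arm has 0 or 10 events. With n = 10 per arm and rate p in both:

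P(fail) = 1 − [1 − p^10 − (1 − p)^10]²

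- p = 1/5: 0.8^10 = 0.107, so 1 − 0.893² = 0.20.
- p = 1/7 or 6/7: (6/7)^10 = 0.214, so 1 − 0.786² = 0.38.
- p = 0.05: 0.95^10 = 0.599, so 1 − 0.401² = 0.84.

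Simulation gave 22%, 38-39% and 83%, in agreement.

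**Arm plus birth weight, gestational age, site and gender.** This model has six parameters with the intercept. In each of 1,000 to 1,500 simulated trials per setting, a linear-programming check asked whether a coefficient vector b exists with s·x′b ≥ 0 for every infant and > 0 for at least one, where s = +1 for an event and −1 otherwise. If so, or if the outcome does not vary at all, no finite estimate exists.

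| Setting, same rate in both arms | Expected size of the rarer outcome class in 20 | Arm alone (formula) | Arm + 4: some coefficient not finite | Arm + 4: arm coefficient not finite |
|---|---|---|---|---|
| Denmark week 1, 6/7 | 20 × 1/7 = 2.9 | 38% | 66-68% | 55% |
| Denmark week 2, 1/7 | 2.9 | 38% | 65-66% | 54% |
| China week 1, 1/5 | 4.0 | 20% | 47% | 34% |
| China week 2, NEC, sepsis (5% assumed) | 1.0 | 84% | 94-95% | 91% |

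**Sensitivity of the five-term model.**
- If gestational age is prognostic (log-odds 1 per SD), the fourth column rises to 75%, 74%, 52% and 96%.
- Control rate 50% against 6/7 in Denmark: 36%, or 45% with prognostic gestational age.
- Control rate 40% against 1/5 in China: 26%, or 36%.
- Control rate 5% against 1/5 in China: 82%, or 86%.
- Rates in the middle in both arms are mostly safe: 11% at 40%, 7% at 50%.

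**All 40 infants in one model** (arm, birth weight, gestational age, gender, country): 12-13% for week-1 intolerance, but 52-58% for week 2. Pooling helps the commoner outcome and does not rescue the rare ones.

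**What a count still gives.** For 0 events in 10, the exact 95% upper limit is 1 − 0.025^(1/10) = 0.31. It is wide, but it is always defined.

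**The case against.** The strongest reply is that the article fixes less than the calculation assumes. The four covariates are introduced as examples and attached to continuous outcomes; for binary outcomes only unspecified confounders are mentioned. A fallback for sparse data could sit in an analysis plan that is not shown. The event rates come from 7 and 5 infants, all treated. The study is a pilot, and raw counts by arm and country would serve much of its purpose.

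Much of this stands, and it is why the result is a range. It does not remove the problem: the article positively prescribes an adjusted model for the binary outcomes, and even arm alone fails in 20-38% of trials at the observed feeding-intolerance rates above zero.

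A reader might infer three stronger points that the documents do not support.
- **That the country split is itself an error and the 40-infant comparison should lead.** The countries differ in control supplement (donor milk or formula), inclusion criteria, feeding regimen and length of intervention, and the Discussion says harmonising the regimens was considered and rejected. Separate comparisons are a reasoned choice. A combined estimate gains precision only by averaging two different contrasts.
- **That siblings will be analysed as independent.** Recruitment and Randomization puts multiples in one arm, "which will be accounted for during the data analysis". The technique is a detail that an article may leave out.
- **That the binary models will usually fail for every outcome.** China week 1 is at about 47%, and mid-range control rates bring the failure share down to about 25-45%.

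**Conclusion.** The concern holds as a limited point about the binary outcomes. Followed as written, with the example covariates and within country, the method has no finite estimate in roughly 45-67% of trials for feeding intolerance at the phase A and B rates above zero, and in about 95% for events near 5%. The share is about 25-45% with mid-range control rates. With arm alone it is about 20-40%, and over 80% at 5%.

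These figures rest on a logit link, the covariate set and distributions stated above, and very small phase A and B samples. All but the mid-range figures also assume equal rates in both arms. The direction is robust; the exact percentages are not. The point is worth correcting because phase C is to inform the next trial, but with no primary endpoint it does not undermine the design.

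**What to change.** Keep the country-specific comparison. In the Randomized Phase C text, replace the multi-covariate model for binary outcomes with one of these:

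- counts per arm and a risk difference with an exact or score interval; or
- Firth-penalised logistic regression with arm and at most one prespecified covariate.

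Report near-zero events such as NEC and sepsis descriptively, as counts per arm and country. Whichever method is chosen must still honour the existing commitment on multiple births.

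A country-stratified estimate on all 40 infants may be added as a supportive analysis beside the country results, not in place of them.

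The cost is a change of wording, which is still open because the article describes phase C as not yet complete. The downside is less covariate adjustment for binary outcomes, so chance imbalance in birth weight or gestational age would have to be judged from the baseline table. Intervals at 10 v 10 will also be wide.
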